### Statistical methods

All continuous variables (anthropometric, biomedical, nutritional and psychological measurements) at baseline and at the primary time point (6-month) will be checked for normality and transformed as needed. The Student *t* test, analysis of covariance (ANCOVA) and multiple linear regression models will be used to assess changes in means before and after the intervention. All tests will be two-sided and *P* values <0.05 will be considered statistically significant.

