**Methods/design:**

This is a four-arm randomized controlled trial. Patients will receive a 6-month intervention and be followed for a further 18 months. Intervention is designed to improve adherence to a healthy diet and/or to increase physical activity, taking advantage of a wrist-based activity monitor. Participants will be recruited among overweight or obese breast cancer patients treated at the European Institute of Oncology, after completion of eventual adjuvant chemotherapy and/or radiotherapy. It is envisaged that 260 patients will be randomized into four arms: Dietary Intervention; Physical Activity Intervention; Physical Activity and Dietary Intervention; and Less Intensive Intervention. Women will be offered individualized counseling consisting of face-to face discussion and phone calls in addition to group meetings. A motivational interviewing approach will be used to encourage health behavior change. All participants will be given a pedometer device to monitor their physical activity. Participants’ dietary intake will be repeatedly assessed using a validated food frequency questionnaire. Participants’ quality of life and anxiety will be assessed with the Functional Assessment of Cancer Therapy-Breast and the State-Trait Anxiety Inventory questionnaires. Blood samples will be collected at baseline and follow-up visits to assess lipid and hormone profiles. Body composition will be repeatedly assessed using bioelectrical impedance vector analysis for identifying changes of fat and fat-free mass. Women allocated to the less intensive intervention arm will be considered as the control group.

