### Sample size

During 2012, 756 overweight or obese women (with a BMI comprising between 25 and 40 kg/m^2^) underwent surgery for early-stage (non-metastatic) breast cancer at the European Institute of Oncology. Data for these patients were retrieved from our institutional breast cancer patients’ database. The mean weight of these 756 patients was 75 kg and the standard deviation was 9.

The sample size calculation was based on a superiority design of any single intervention (DI, PAI, or PADI) compared to the control group (LII). A sample group of 65 patients (control group) and similar number in any of the three intervention groups (diet and/or exercise) for a total of 195 patients achieve 80 % power to detect a 5 % weight loss (3.75 kg) between the null hypothesis that both group means are 75 kg and the alternative hypothesis that the mean of any of the intervention group 2 is 71.25 after 6 months, with known group standard deviations of 9.0 and 9.0 and with a significance level (alpha) of 0.05 using a two-sided two-sample *t* test. We have foreseen a drop-out of 5 % over the first 6 months.

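### The Statistical methods section aims its tests at before-after change rather than each intervention versus LII; a between-arm ANCOVA on baseline weight should be named primary

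*Protocol article*

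**What the plan says.** All references are to the protocol article.

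- **Statistical methods.** The Student t test comes first in the list, followed by "analysis of covariance (ANCOVA) and multiple linear regression models will be used to assess changes in means before and after the intervention". No method is ranked and no contrast between arms is given. Continuous variables of every kind "will be checked for normality and transformed as needed".
- **Sample size.** The hypothesis is between arms: a "superiority design of any single intervention (DI, PAI, or PADI) compared to the control group (LII"). It is powered at 80% with a two-sided two-sample t test at alpha 0.05, on the alternative that "the mean of any of the intervention group 2 is 71.25 after 6 months" against 75 kg in control, "with known group standard deviations of 9.0 and 9.0". That SD comes from a hospital database: "The mean weight of these 756 patients was 75 kg and the standard deviation was 9". It is therefore the spread of body weight between women, not the SD of change.
- **Statistical considerations.** LII is named as the control group.
- **LII arm and Intervention.** LII women receive general counselling to lose weight and two motivational calls. Women in all four arms wear the activity monitor.
- **Measures and Table 1.** Weight is measured at baseline and at 6 months in every participant.

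**The concern.** The stated target of the analysis and the stated hypothesis differ. A before-after test asks whether one arm's mean weight moved. The trial asks whether an intervention arm moved more than LII. Because LII is itself advised to lose weight, a fall in all four arms is plausible, and a significant fall within an intervention arm would say nothing about the added effect of the intervention. Comparing P values across arms, significant here and not there, does not repair this.

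Precision is also at stake. The one powered method takes raw 6-month weight and leaves out the baseline weight collected from every woman. A baseline-adjusted comparison is already on the article's list, but nothing makes it the one that decides.

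**Working it through.** **Inputs.** From the Sample size section: difference 3.75 kg (75 minus 71.25), SD 9 kg, two-sided alpha 0.05, 65 women per arm, 5% dropout. Completers: 65 × 0.95 = 61.75, taken as 62. Assumed, because the article does not give it: the baseline to 6-month weight correlation r, shown over a range, with the same SD of 9 kg at both times.

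**Step 1: the plan's own figure.** Standard error of a difference between two arms = SD × √(2/n).

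- n = 65: 9 × √(2/65) = 1.579; 3.75/1.579 = 2.38; power 65.5% (noncentral t; 66.1% by normal approximation).
- n = 62: 9 × √(2/62) = 1.616; 3.75/1.616 = 2.32; power 63.4%.
- n for 80% power: 2 × (1.960 + 0.842)² × (9/3.75)² = 2 × 7.85 × 5.76 = 90.4, so 91 per arm; 91/0.95 gives 96 with dropout.

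The 80% does not reproduce for one arm against LII. It does reproduce if the three intervention arms are pooled against LII: (1 + 1/3) × 7.85 × 5.76 = 60.3, so 61 controls; 61/0.95 gives 65 controls and 3 × 65 = 195 intervention patients, 260 in all. That matches the Abstract's "It is envisaged that 260 patients will be randomized into four arms", but it is not the comparison the section describes.

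**Step 2: adjusting for baseline.** The ANCOVA residual SD is 9 × √(1 − r²). The change-score SD is 9 × √(2(1 − r)). Power for 3.75 kg with 62 per arm:

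| r | ANCOVA SD | ANCOVA, alpha 0.05 | ANCOVA, alpha 0.0167 | Change SD | Change-score t test, alpha 0.05 |
|---|---|---|---|---|---|
| 0.5 | 7.79 | 76% | 60% | 9.00 | 63% |
| 0.6 | 7.20 | 82% | 68% | 8.05 | 73% |
| 0.7 | 6.43 | 90% | 79% | 6.97 | 84% |
| 0.8 | 5.40 | 97% | 92% | 5.69 | 95% |
| 0.9 | 3.92 | >99% | >99% | 4.02 | >99% |

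Alpha 0.0167 is 0.05/3, a Bonferroni adjustment for three comparisons with LII.

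**Step 3: correlation needed for 80% power.** With 62 per arm, r must be about 0.57 at alpha 0.05 (0.56 by normal approximation) and about 0.70 to 0.71 at alpha 0.0167.

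**Step 4: ANCOVA against change score.** 1 − r² = (1 − r)(1 + r), which is never more than 2(1 − r). Apart from one degree of freedom, ANCOVA is therefore at least as precise as the change score, and the two converge as r approaches 1.

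**Step 5: what a within-arm test would show.** Suppose all four arms lose the same amount, with a change SD of 4 kg (both assumed; this SD corresponds to r of about 0.9) and 62 per arm. For a 1.5 kg loss, 1.5/(4/√62) = 2.95 and each before-after test is significant about 83% of the time. For a 1 kg loss, 1/(4/√62) = 1.97 and the figure is about 49%, so two given arms would disagree about half the time: 2 × 0.49 × 0.51 = 0.50. In neither case is there any difference between arms.

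**The case against.** The strongest reply is that the sentence is loose rather than wrong. It does not say within-arm or paired. ANCOVA is already listed, and its usual role in a trial is to compare arms. The Sample size section, the Statistical considerations and the Discussion all frame the comparison against a common control. Comparing changes between arms is a natural reading. A condensed article may also leave the choice of primary model to an analysis plan that is not shown. This stands in part. A reader might infer that the sponsor intends to claim efficacy from within-arm P values, but the article does not say so. What remains is that the one sentence defining the analysis names a target other than the trial's hypothesis, so a literal reader could follow it to the wrong test.

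Three further inferences go beyond the text:

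- **That the planned analysis throws away baseline weight.** Analysing change uses baseline, and ANCOVA is listed. The 63% at 62 per arm belongs to the sample-size method. Against a between-arm change score the gain is modest at high r: 84% to 90% at 0.7, and 95% to 97% at 0.8.
- **That ANCOVA restores the stated power.** This depends on r, which is not given, and on LII losing nothing. If LII lost 1.5 kg and an intervention arm 3.75 kg, the difference would be 2.25 kg, and ANCOVA power with 62 per arm would be 49%, 63% and 89% at r = 0.7, 0.8 and 0.9.
- **That the normality check is a plan to choose the scale of the primary effect after seeing results.** The wording is generic and covers biochemical, nutritional and psychological variables as well.

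**Conclusion.** The point holds as a mismatch between the analysis sentence and the between-arm hypothesis, with a concrete improvement available. It does not show that the sponsor plans an invalid test. The unadjusted t test on which the trial was sized has 63 to 66% power for a single arm against LII, about 14 to 17 points below the stated 80%. Baseline-adjusted ANCOVA brings this to between 76% and more than 99% for r from 0.5 to 0.9, assuming a true difference of 3.75 kg, SD 9 kg at both times and 62 completers per arm. It reaches 80% only if r is at least about 0.57, or about 0.70 to 0.71 with Bonferroni adjustment. Correlations of that size are plausible for repeated body weight, but they remain an assumption here. The Sample size figure stays wrong for the comparison it describes, and ANCOVA does not correct it.

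**What to change.** Replace the sentence in Statistical methods with one named primary analysis: ANCOVA of 6-month weight in kg, untransformed, on arm with baseline weight as covariate, reporting each intervention-minus-LII difference with its confidence interval. State that within-arm P values are descriptive and not evidence of efficacy. An unadjusted between-arm t test can stay as a sensitivity analysis.

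The cost is one paragraph, with no new data and no extra patients. It also requires a decision: Study outcomes and Statistical considerations express the primary outcome as a loss of at least 5% of baseline weight, so the sponsor must say that mean weight is the primary scale and the threshold secondary. Analyses are planned only after the end of the trial, so the decision can be made before any outcome comparison.

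Two matters need their own correction: the 80% power figure in Sample size, and a rule for three comparisons each at 0.05 (familywise error about 1 − 0.95³ = 14% if they were independent).

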### Dissemination policy

The final report will be presented at the Associazione Italiana per la Ricerca sul Cancro (AIRC). Trial results will be communicated to participants organizing a dedicated event. Results will be also communicated in peer-reviewed journals, in national and international scientific conference, and to the public via press release.

### Data collection, storage and security

All data collected on the questionnaires and all relevant information about the participants will be uploaded on dedicated electronic databases. All forms must be filled in by the researcher or by a person delegated by the researcher. Data will be held according to the International Conference on Harmonisation (ICH) Good Clinical Practice (GCP) E6 Guideline and the Declaration of Helsinki and will be treated with confidentiality, following the current privacy policy [46].

Fully anonymized data from the EPIC food frequency questionnaire will be uploaded on a dedicated online database [47] for the conversion of the FFQ data into a list of food-group and nutrient intake. Data recorded by the pedometer device will be downloaded on a dedicated application [48] adopting security measures to protect personal information [49]. Fully anonymized data will be conveyed periodically to researchers and saved to a password-protected server.

### Registration

The trial is registered with ClinicalTrials.gov, number NCT02622711 (registration date: 2 December 2015) and with ISRCTN registry, number ISRCTN53325751 (registration date: 16 October 2015).

## Discussion

We presented the protocol of a 6-month intervention trial focused on weight loss in a group of overweight or obese women previously treated for early breast cancer. This trial will provide important insights regarding the effect of an intervention carried out in Italy which is designed to improve adherence to a healthy diet and/or to increase physical activity and decrease sedentary time, taking advantage of a pedometer device. Despite the increasing number of trials of weight loss interventions in breast cancer, so far only the DIANA (DIet and ANdrogens) randomized controlled trials have been undertaken on cancer survivors in Italy. They studied the effect of a Mediterranean-macrobiotic lifestyle on breast cancer patients [50] and found a 10 % reduction of testosterone level [50] and an improvement of cardiopulmonary functional capacity and vascular endothelial function following a moderate intensity exercise training combined with the macrobiotic diet [51]. The most recent extension of the DIANA trial [52] is ongoing. It is a two-arm intervention to promote dietary change and a moderate increase in physical activity aimed at decreasing circulating hormone concentrations, breast cancer recurrences, and improving survival.

Our study, with its multi-arm design, has the advantage of evaluating the effect on participants by comparing three different approaches to a common control arm or combining the effect of the interventions. It also appears more appealing to patients because it provides an increased probability of receiving an experimental intervention rather than the control treatment. The educational components of our intervention will be based on national [35] and international recommendations [4], promoting the Mediterranean diet, which includes many dietary features that have been shown to promote health [53]. The scheduled visits and the motivational interviewing approach chosen should ensure a more active role of the patients in lifestyle change to achieve success. Motivational interviewing aims to enhance self-efficacy and personal control for behavior change. It uses an interactive, empathic listening style to increase motivation and confidence, emphasizing the discrepancy between personal goals and health behaviors [54]. Moreover our project will take advantage of a pedometer device to quantify ambulatory activity during walking and running, by means of a common and easily understood metric (i.e., steps). This device is appealing since it objectively monitors physical activity and can be an important means for providing behavioral feedback and motivation. Pedometer-based walking interventions have demonstrated their effectiveness in increasing physical activity in adult populations [55–57]. Objective measuring changes in physical activity in addition to a standard measurement (questionnaire) can add further precision to the physical activity level reached by participants during the intervention.

Due to the increasing concern on the role of obesity in cancer survival and recurrence [11], there is the need for evidence regarding the most effective approach in promoting weight control and the adoption of a healthy lifestyle in breast cancer survivors. The results of this innovative project will provide useful information for future interventions and potentially have a large public health impact on breast cancer survivors.

## Trial status

Recruitment started in November 2015 and is ongoing.

## Abbreviations

BCM, body cell mass; BIVA, bioelectrical impedance vector analysis; BMI, body mass index; CRP, C-reactive protein; DI, dietary intervention; ECW, extracellular water; EPIC, European Prospective Investigation into Cancer and Nutrition; ER, estrogen receptor; FACT-B, Functional Assessment of Cancer Therapy-Breast; FFM, fat-free mass; FFQ, food frequency questionnaire; FM, fat mass; HDL, high-density lipoprotein; HER2, human epidermal growth factor receptor 2; IEO, European Institute of Oncology; IGF, insulin-like growth factor; IPAQ, International Physical Activity Questionnaire; kcal, kilocalorie; LDL, low-density lipoprotein; LII, less intensive intervention; MET, metabolic equivalent; PADI, physical activity and dietary intervention; PAI, physical activity intervention; QoL, quality of life; R, resistance, Ohm; STAI, State-Trait Anxiety Inventory; TBW, total body water; VLDL, very low density lipoprotein; Xc, reactance; Z, vector.
